### Analysis plan

For the primary analysis, patient-rated low back pain will be analyzed at 12, 26, and 52 weeks with linear mixed model regression to estimate mean differences between treatment groups at each time point adjusting for baseline covariates (i.e., rank-order minimization variables) and accounting for correlation across measurements within person. Short- and long-term longitudinal effects between groups will also be assessed using mixed model analyses including LBP intensity outcomes from weeks 4 to 12 and weeks 4 to 52, respectively. Due to the longitudinal study design, the primary analysis plan was modified from a one-way analysis of covariance to a linear mixed model approach to allow increased flexibility when specifying a variance-covariance structure and accounting for missing data [58-60]. The analysis plan was modified prior to the completion of data collection and the start of data analysis.

The variance-covariance structure that best fits the data will be used to account for correlation among the repeated measurements within participants [61,62]. Normality assumptions will be evaluated through normal probability plots and transformations used, if necessary. We will test for a site-by-group interaction, but given our standardization plan, we do not expect it to be present. Adjusted mean differences and 95% confidence intervals between groups for short- and long-term effects based on the final models will be presented in tables and line graphs. The need for inclusion of additional covariates to balance baseline group differences will be evaluated in sensitivity analysis. Intention-to-treat analysis will be used; all patients with at least one follow-up measure will be included in the analysis as the methods do not require data at every time point. In the event that missing data is present, the pattern of missingness will be assessed and appropriate imputation and sensitivity analyses will be performed. Responder analyses (i.e., 50, 75, and 100% pain reduction) will be conducted to facilitate the interpretation of the results [63-65].

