### Power analysis and sample size

The basis for our sample size calculation is the one-way analysis of covariance (ANCOVA), comparing the primary outcome (reported pain level at the 12, 26, and 52 week time points) between groups and adjusting for baseline pain level. We estimated the standard deviation for change in pain using data from the trial by Jones et al [18] (SD = 1.4). A conservative R^2^ estimate of 0.2 was used for the sample size calculation. With a power of 0.92 and a 2-group design tested at an alpha level of 0.01, 80 subjects per group are required to detect a pain reduction of 0.8 points (Power and Precision™ 2.0). We will allow for a dropout rate/loss to follow-up of up to 15%. Therefore, 92 patients are required per group, for a total of 184 subjects.

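### Choosing the primary model's covariance structure by its fit to the trial data can make standard errors at single time points wrong; an unstructured matrix fixed in advance avoids this at almost no cost

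*Protocol article*

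**What the plan says.** All but one of the relevant statements are in the protocol article's Analysis plan.

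- **Primary model:** "patient-rated low back pain will be analyzed at 12, 26, and 52 weeks with linear mixed model regression", giving a mean difference between groups at each of the three time points, adjusted for the minimization variables.
- **Covariance rule:** "The variance-covariance structure that best fits the data will be used". Its stated purpose is to model the dependence between a person's repeated scores.
- **Reason for moving from ANCOVA to a mixed model:** among others, "to allow increased flexibility when specifying a variance-covariance structure and accounting for missing data".
- **Additional models:** short- and long-term longitudinal effects, using "LBP intensity outcomes from weeks 4 to 12 and weeks 4 to 52, respectively".
- **Reporting:** "Adjusted mean differences and 95% confidence intervals between groups". These are to come from whichever models are finally chosen.

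The one significance level in the article is in Power analysis and sample size, where the design is "tested at an alpha level of 0.01". That section also gives the only SD, 1.4 for change in pain, with none per visit.

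**The concern.** The rule makes the standard errors of the primary contrasts depend on a choice made after the data are seen. Because the plan wants a separate group difference at each visit, the variance at each visit matters directly. Compound symmetry and first-order autoregression, two common candidates, assume the same variance at every visit. A criterion that rewards parsimony can prefer them even when the true variances differ moderately. Each visit's standard error then comes from a pooled variance.

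If pain is more variable at week 52 than at week 12, the week-52 interval is too narrow and the week-12 interval too wide. Both are primary time points. Study treatment, and the request not to seek other care for low back pain, cover only the first 12 weeks, so participants could plausibly diverge by one year. The article gives no data on this, and a falling spread is also possible.

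**Working it through.** **1. The plan's own figure.** Inputs from Power analysis and sample size: difference 0.8, SD 1.4, R² 0.2, alpha 0.01 (taken as two-sided), power 0.92.

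n per group = 2 × (2.576 + 1.405)² × 1.4² × (1 − 0.2) / 0.8² = 77.7, so 78. The article states 80, and an ANCOVA calculation with the noncentral t distribution gives power 0.922 at 80 per group. The figure is reproduced. It rests on one SD and says nothing about how the SD varies over visits.

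**2. What a common variance does.** Assume SDs of 1.8, 2.0 and 2.2 at weeks 12, 26 and 52. These are not in the article.

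- Variances: 3.24, 4.00, 4.84. Pooled: (3.24 + 4.00 + 4.84) / 3 = 4.03.
- The ratio of the SE used to the correct SE is √(pooled variance / visit variance).
- The actual two-sided error is 2 × [1 − Φ(critical value × ratio)].

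| Visit | SE ratio | Error at nominal 0.05 | Error at nominal 0.01 |
|---|---|---|---|
| Week 12 | 1.115 | 0.029 | 0.004 |
| Week 26 | 1.003 | 0.049 | 0.010 |
| Week 52 | 0.912 | 0.074 | 0.019 |

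For week 52 at 0.01: 2.576 × 0.912 = 2.35, two-sided 0.019. These are the errors if a common variance is always used.

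**3. How often selection leads there.** Simulation under no effect used three visits, 80 per group, complete data, REML-type fits and model-based standard errors. The candidates were compound symmetry, AR(1) and unstructured. With SDs 1.8/2.0/2.2:

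- **BIC:** a common-variance structure is chosen in 85 to 90% of runs. Week-52 error is 0.065 to 0.071 at 0.05 and 0.016 to 0.019 at 0.01. Week-12 error is 0.030 to 0.036 at 0.05.
- **AIC:** week-52 error is about 0.05 to 0.056 at 0.05 and about 0.012 at 0.01.

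**4. How it varies with the assumptions.** Week-52 error at nominal 0.01 in the three-visit model, with SDs anchored on 1.4 and correlations from 0.3 to 0.7:

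| Scenario | Error |
|---|---|
| Equal SDs | 0.0098–0.010 |
| SD rising to 1.6–1.8, BIC, three candidates | 0.015–0.0185 |
| Same SDs, AIC | 0.011–0.013 |
| Same SDs, heterogeneous CS and AR(1) added, BIC | 0.012–0.0155 |
| Same SDs, heterogeneous forms added, AIC | 0.010–0.012 |
| Steeper rise, 1.4/1.7/2.0, selection free to reject equal variance | 0.010–0.013 |
| SD falling over time | 0.005–0.010 |
| 92 per group with 15% dropout, SD rising to 1.7, BIC, three candidates | 0.017–0.019 |
| As above, AIC | 0.011 |

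A moderate rise is the unfavourable case: a small one does little harm, and a large one is detected. Only if the list held no unequal-variance form at all would steeper rises matter more (0.026 at 1.4/1.7/2.0).

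**5. After the fix.** With an unstructured matrix fixed in advance, week-52 error is about 0.010 at nominal 0.01 in every scenario, because the week-52 standard error then uses the week-52 variance. It needs 3 × 4 / 2 = 6 covariance parameters for three visits and 5 × 6 / 2 = 15 for five, with about 160 to 184 participants.

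**The case against.** The strongest reply is that candidate lists, selection criteria and fallback orders belong in a statistical analysis plan, and a journal article may leave them there. That stands: their absence is not a fault. But the article goes further and states a positive rule, selection by fit to the trial data, and that rule is what this point addresses.

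A second reply is that choosing a covariance structure by fit is accepted practice, and that on raw likelihood the unstructured matrix always fits at least as well as the simpler forms. One literal reading of the rule therefore already gives the recommended model. This also stands in part. It shows that the rule can be harmless, and that the outcome turns on something the wording leaves open.

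Three stronger readings are tempting, and the article supports none of them.

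- **That the false-positive rate at week 52 is about 0.02.** This lies at the top of the range and needs rising SDs, a BIC-type criterion and a narrow list, none of which the article states.
- **That the weeks 4 to 52 model makes matters worse.** With rising SDs, BIC and the narrow list, five-visit simulations give 0.017 to 0.028 at nominal 0.01. But the article takes the primary difference at week 52 from the three-visit model and does not say that a week-52 test will come from the longer one.
- **That the reported interval is a 0.01-level interval.** The 0.01 level appears only in the sample-size section; the Analysis plan reports 95% intervals. The concern does not depend on 0.01, but interval coverage has to be judged at 95%.

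**Conclusion.** The point holds as a conditional one. The stated rule allows a common-variance structure to set the standard errors of visit-specific primary contrasts. Where variances differ between visits, those errors are then too small at some primary time points and too large at others.

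For the three-visit primary model with moderately rising SDs, week-52 type I error is about 0.055 to 0.07 at nominal 0.05 (95% interval coverage about 93 to 94.5%) and about 0.010 to 0.019 at nominal 0.01. The SDs per visit, correlations, candidate list, criterion and use of model-based standard errors are all assumptions. AIC or heterogeneous candidates bring the error close to nominal, and equal SDs give no inflation. Falling SDs make week 52 conservative and the first visit liberal.

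This is a cheap improvement to a stated method. It does not show that the trial's result would be wrong.

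**What to change.** In the Analysis plan, replace selection by best fit with a prespecified unstructured covariance matrix, common to both groups, with Kenward-Roger degrees of freedom. Apply it to the 12/26/52-week primary model and likewise to the longitudinal models. State the fallback order if the model does not converge, using only structures that let the variance differ by visit: for example heterogeneous Toeplitz, then heterogeneous AR(1).

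The cost is one or two sentences and a few more covariance parameters: 6 for three visits, against 2 for compound symmetry or AR(1). The loss of power is negligible at this sample size. The mixed model's handling of missing visits, one of the plan's reasons for adopting it, is kept.

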### Power analysis and sample size

The basis for our sample size calculation is the one-way analysis of covariance (ANCOVA), comparing the primary outcome (reported pain level at the 12, 26, and 52 week time points) between groups and adjusting for baseline pain level. We estimated the standard deviation for change in pain using data from the trial by Jones et al [18] (SD = 1.4). A conservative R^2^ estimate of 0.2 was used for the sample size calculation. With a power of 0.92 and a 2-group design tested at an alpha level of 0.01, 80 subjects per group are required to detect a pain reduction of 0.8 points (Power and Precision™ 2.0). We will allow for a dropout rate/loss to follow-up of up to 15%. Therefore, 92 patients are required per group, for a total of 184 subjects.

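### 184 participants preserve the required 80 per group only up to 13% loss, not the stated 15%

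*Protocol article*

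**What the plan says.** All the figures stand in the section Power analysis and sample size of the protocol article. The calculation is based on an analysis of covariance of pain, adjusted for baseline pain, with a standard deviation for change of 1.4. On the covariate it says: "A conservative R^2^ estimate of 0.2 was used for the sample size calculation". The design parameters and the resulting number are given as "With a power of 0.92 and a 2-group design tested at an alpha level of 0.01" and "80 subjects per group are required to detect a pain reduction of 0.8 points". The next two sentences set the margin for attrition, "We will allow for a dropout rate/loss to follow-up of up to 15" per cent, and the enrolment target, "Therefore, 92 patients are required per group, for a total of 184 subjects". The inflation formula is not written out. The figure of 184 is repeated as the size of the trial in the Abstract and under Study aims, but it is justified only here.

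**The concern.** The enrolment target is presented as the consequence of two preceding numbers: 80 evaluable per group and up to 15% loss. A dropout rate applies to the people enrolled. The number enrolled, multiplied by the proportion retained, must therefore give back at least 80. With 92 per group it does not.

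Two things are at stake. First, the sample size, the attrition allowance and the power of 0.92 are not consistent with one another at the edge of the stated allowance. Second, readers of the results will judge actual attrition against the 15% margin. A loss between 13% and 15% would be described as within plan although the required 80 per group had not been reached.

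**Working it through.** **Inputs, all from Power analysis and sample size**

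- Evaluable participants per group: 80
- Allowed loss: 15%
- Enrolled: 92 per group, 184 in total
- Difference to detect: 0.8 points
- SD of change: 1.4
- R²: 0.2
- Alpha: 0.01, with sidedness not stated
- Power: 0.92

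**Step 1. Reproduce the base figure of 80.**

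Residual SD = 1.4 × √(1 − 0.2) = 1.252. For a total of N participants in two equal groups with one covariate, the noncentrality parameter is 0.8 / (1.252 × √(4/N)) on N − 3 degrees of freedom. With N = 160 it is 0.8 / (1.252 × 0.1581) = 4.04 on 157 degrees of freedom. At two-sided alpha 0.01 this gives power 0.9225, matching the stated 0.92. At 79 per group power is 0.9187, so 80 is the smallest number per group that reaches 0.92.

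Two-sided testing is an assumption, but the alternatives do not give 80. By the normal approximation, a one-sided test needs 69 per group, and a two-sided test that ignores R² needs 98. The base figure is therefore sound, and the problem lies only in the inflation step.

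**Step 2. Reproduce the enrolled figure of 92.**

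80 × (1 + 0.15) = 92.0. The match is exact, so multiplication is the likely route, although the article does not show it.

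**Step 3. Check the enrolled figure against the stated loss.**

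| Quantity | Calculation | Result |
|---|---|---|
| Left per group after 15% loss | 92 × 0.85 | 78.2 |
| Left in total after 15% loss | 184 × 0.85 | 156.4 (160 required) |
| Loss that 92 per group can absorb | 1 − 80/92 | 13.0% |
| Enrolment that keeps 80 per group at 15% loss | 80 / 0.85 | 94.1, so 95 per group or 190 in total |
| The same, inflating the total and rounding once | 160 / 0.85 | 188.2, so 189 in total |

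In whole people, 92 per group leaves room to lose 12, while 15% of 92 is 13.8. The gap is about 2 evaluable participants per group. Expressed as enrolment it is 3 per group (6 in total), or 5 in total if rounded once.

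**Step 4. Consequence for power at 15% loss (two-sided alpha 0.01).**

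| Per group | Noncentral t | Normal approximation |
|---|---|---|
| 80 | 0.9225 | 0.929 |
| 78 | 0.9147 | 0.921 |

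The loss is 0.9225 − 0.9147 = 0.008 by the noncentral t method, which is the one that reproduces 80. The normal approximation loses 0.929 − 0.921 = 0.008 as well.

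**The case against.** The strongest reply is that almost nothing changes. Power stays above 0.91 at a strict alpha of 0.01. Whether it reads 0.91 or 0.92 turns on rounding: 78 per group gives 0.9147, while the unrounded 78.2 gives 0.9155. This stands. The finding should rest on the 15% allowance and not on the second decimal of the power.

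A second reply is that the Analysis plan replaced analysis of covariance with a linear mixed model that includes everyone with at least one follow-up measure. A participant lost late still contributes earlier pain scores, so 15% lost by week 52 does not remove 15% of the information. This is true and softens the practical effect. It does not repair the statement, because the sample size section still rests on analysis of covariance and nowhere claims that the mixed model covers the gap. Participants with no follow-up measure are excluded under either method.

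A third reply is that 15% might have been meant as a fraction of the 80 evaluable: 0.15 × 80 = 12, and 80 + 12 = 92. That may be how the number arose, but a dropout or loss rate is ordinarily counted among those enrolled, and that is how readers will compare it with observed attrition.

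Finally, the route by multiplication is inferred. The shortfall does not depend on it, since 92 × 0.85 is below 80 whatever formula was used. Nor can the full protocol or an analysis plan alter the result, because all three numbers are printed here.

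**Conclusion.** The concern holds: the statement is wrong as written and minor in size. By the article's own figures, 184 participants preserve 80 per group with up to 13.0% loss, and at 15% loss about 78 per group remain. This part is plain arithmetic and needs no assumption beyond reading the loss rate as a share of those enrolled. The power figure of about 0.915 at 78 per group, against 0.922 at 80, also assumes a two-sided test, equal loss in both groups, and the single-covariate analysis of covariance on which the sample size is based. The validity of the trial is not in question.

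**What to change.** Keep 184 and correct the sentence in Power analysis and sample size, for example:

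> Enrolling 92 participants per group (184 in total) preserves 80 per group with loss to follow-up of up to 13%. At 15% loss about 78 per group remain, and power for the analysis of covariance at two-sided alpha 0.01 is about 0.91.

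The two-sided wording should be confirmed by the trial's statistician, since the article does not state it. Any later report should compare observed attrition with 13%.

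The cost is one sentence and a slightly less favourable stated margin. Enrolling 95 per group (190 in total) would make the 15% claim true, but a loss of under one percentage point of power does not call for it, and no extra enrolment is proposed.

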### Data and safety monitoring

The Office of Data Management at Northwestern Health Sciences University serves as the data coordinating center responsible for creation of data collection forms, coordination of data transfer, and data management. A Data Safety and Monitoring Committee consisting of study and non-study clinicians and scientists meet annually to review the study. Due to the low risk profiles of the study interventions no interim analyses are planned. Adverse events are classified using the National Institutes of Health Office of Human Subjects Research definitions [66].

## Discussion

LBP is a significant health problem not only for adults, but also for children and adolescents. Given the large social and economic costs associated with the condition, identifying effective, conservative management strategies is critical. While SMT and exercise have been shown to be effective in adult populations, high quality research is needed to investigate their effectiveness in adolescent LBP patients.

Only a limited number of interventions for adolescent LBP have been evaluated in clinical trials; consequently, there is no established ‘gold-standard’ treatment. We chose exercise as a core intervention because of the evidence of effectiveness for adults with LBP [15,16], in addition to the preliminary evidence in adolescent populations [67]. Further, we wanted to encourage active behaviors for the management of pain in an adolescent population. We hypothesized that adding SMT to a promising treatment like exercise will produce greater improvements in LBP than what will be achieved by exercise alone.

Given there have been few studies addressing LBP in adolescents (and there have been no randomized clinical trials of SMT), we designed this trial with sufficient methodological rigor to maintain high internal validity; however, where possible, we also included pragmatic design features to enhance generalizability [68]. Explanatory design aspects of the trial aimed at ensuring high validity and low risk of bias include: the use of multiple baseline assessments to ensure participant compliance; eligibility criteria to exclude individuals unlikely to demonstrate treatment effects (e.g., pain intensity ≥ 3/10); restricted utilization of co-interventions during the intervention phase; structured protocols for the application of the intervention (number of visits, exercise, or SMT techniques used); application of the intervention at university-associated research clinics by clinicians with investigator supervision; and monitoring of participant and provider compliance including strategies to maximize adherence to study protocols. Pragmatic features of the study include: multiple recruitment sources from the general population at multiple sites; flexibility in the application of the intervention (e.g., exercise progressions, type of SMT used) based on individual patient needs and abilities; the use of an active treatment comparison group; the collection of both short- and long-term outcomes; and the plan to use intention-to-treat statistical analysis.

Upon completion, this study will provide high quality scientific evidence regarding SMT and exercise for LBP in adolescents with the potential to alter clinical practice and reduce both the current and future burden of LBP.
